#### 2.1.1. Inclusion Criteria

Patient must be ≥18 years and have survived an OHCA with attempted resuscitation by the Emergency Medical System. They display a **CPC 1–2 or mRS ≤ 3** at discharge and are capable of providing written informed consent.

#### 2.1.2. Exclusion Criteria

Patients unable to speak the language to a sufficient degree to be able to participate in the assessments will not be recruited. In addition, patients with acute, currently unresolved psychological disorders of moderate/severe intensity—e.g., major depression, schizophrenia—will not be recruited in this trial.

#### 2.1.3. Enrolment and Assessments

The Lombardia CARe Registry records all admissions of patients who have suffered an out-of-hospital cardiac arrest across seven provinces in the Lombardy region, updated to the previous 24 h. This registry is monitored daily by the team involved in this study; for patients admitted to the IRCCS Policlinico San Matteo Hospital in Pavia, their clinical history (including survival and neurological status) is monitored via the hospital internal electronic system and, if eligible, they are approached to provide consent for participation to this study close to their discharge day, usually in the cardiology ward. For those patients admitted to one of the ten other main recruiting hospitals (Figure 1), the local investigator will approach them for screening and enrollment. They will also inform the study team about their clinical status and readiness for assessment before hospital discharge. To minimize the risk of patients being missed, an email will be sent to all the investigators of the main recruiting hospitals every Monday and every Friday. The secondary recruiting centres do not have an allocated local investigator, so they will be contacted as and when required.

Most eligible patients are supposed to be approached before hospital discharge; if not, the study management team will contact them within 15 days post-discharge. Following informed consent, baseline assessment will be conducted by a clinical psychologist, either in-person (for patient admitted to Fondazione IRCSS San Matteo hospital, Pavia) or remotely (via telephone call or telemedicine, for all other patients), using measures of cognitive ability (Montreal Cognitive Assessment [22]), anxiety and depression [23], health-related quality of life [24], and symptoms of post-traumatic stress disorder [25]. Parallel versions of the cognitive assessment will be administered to reduce practice effects. A list of all measures and their purpose is described in Table 2.

In addition to quantitative instruments, starting from the first follow-up after hospital discharge (that is, the 1-month follow-up), patients will also undergo a brief semi-structured, qualitative interview focused on their own subjective experience of returning to day-to-day life, fatigue, cognitive problems, mood difficulties, and their ability to access appropriate information/support about their condition (Appendix A; Table A1).

### 2.2. Criteria for Feasibility and Acceptability

Feasibility will be defined quantitatively by examining the **recruitment rate** (i.e., the proportion of eligible patients who consent to participate) and the **retention rate** (i.e., the proportion of enrolled patients who complete scheduled follow-up assessments over the 12-month period). In the absence of literature benchmarks and prior pilot data, a pragmatic threshold *of 80% recruitment rate* of eligible patients will be set as a measure of feasibility.

Acceptability will be operationalized as an *overall retention rate of 50% or more of the recruited patients* over 12 months. In addition, this study will look at feasibility and acceptability by follow-up modality, comparing the recruitment and attrition rates between face-to-face assessments at the main hospital and remote assessments at the other hospitals. A significantly lower recruitment rate or higher attrition rate in the remote modality, as compared to the face-to-face approach, will be interpreted as indicative of reduced feasibility and acceptability.

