## 2. Materials and Methods

### 2.1. Study Design

This is a prospective, multicenter observational protocol, spanning 24 months, across 22 hospitals affiliated with the Lombardy Cardiac Arrest Registry (“Lombardia CARe”—a full list of the hospitals is provided in Table 1). This network covers a population of approximately 4.3 million people and includes densely populated urban areas and sparsely populated rural and mountainous locations.

In the REVIVE project, each of the 22 hospitals will have a named contact person (usually a senior cardiologist) who will enroll eligible survivors and inform the study team of the clinical status and readiness to be assessed before hospital discharge. Based on registry data from 2022, >90% of patients with a good neurological outcome (CPC 1–2; mRS ≤ 3) were discharged from 11 hospitals affiliated to this network, therefore these sites have been highlighted in Table 1 as ‘Main Recruiters’ and a picture describing their approximate location in the Lombardy region is provided (Figure 1).

The REVIVE project plans to enroll consecutive OHCA survivors meeting eligibility criteria and to follow them up for 12 months post-discharge. Survivors will be assessed at five different timepoints: **T0**—before discharge (or within 15 days post-discharge); **T1**: 1 month post-discharge; **T2**: 3 months post-discharge; **T3**: 6 months post-discharge; **T4**: 12 months post-discharge.

At each time point, the same battery of questionnaires will be administered **in-person or over the telephone/via telemedicine**, based on patient preference and feasibility.

Should a significant need be identified, the study team will, in the first instance, consider whether psychological therapy/cognitive rehabilitation can be provided in-house; however, it is expected that most patients will be referred to community-based rehabilitation programmes or other specialists where required.

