Longitudinal changes in HADS, MoCA, EQ-5D-5L, and IES-R from T0 to T4, as well as differences in the retention rate between patients seen remotely or face-to-face, will be analyzed using mixed-effects models (linear or logistic) incorporating time and potential covariates (e.g., age, sex, comorbidities). Models will initially include random intercepts and slopes at participant and hospital levels. Different residual covariance structures (e.g., first-order autoregressive [AR(1)]) will also be explored. Model selection will be guided by the Akaike Information Criterion (AIC) and Bayesian Information Criterion (BIC); simpler random intercept-only models will be adopted if convergence issues arise. Missing data will be handled using Multiple Imputation by Chained Equations (MICE), assuming a Missing At Random (MAR) mechanism. Twenty imputed datasets will be generated, incorporating all key predictors and outcomes, as well as hospital ID. Participants who completely withdraw from this study will be treated as censored at their last observation without further imputation. Sensitivity analyses comparing complete-case and imputed datasets will be conducted to assess the robustness of the findings. A *p*-value < 0.05 (two-sided) will denote statistical significance.

Qualitative data will be derived from detailed notes taken during semi-structured interviews; the analysis will employ a framework approach, well-suited for applied qualitative research with pre-defined areas of inquiry [29]. The analytic process will involve familiarization with the notes, followed by the development of a thematic framework based on the predetermined domains. Data will then be indexed using both deductive codes—stemming from the interview guide—and emergent codes that may arise from the content of the notes. A matrix will be constructed to chart responses across cases, enabling systematic cross-case comparisons.

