## 4. Discussion

Survivors of OHCA face a broad array of challenges, extending beyond the immediate physical aftermath to include psychological distress, cognitive impairments, and chronic fatigue. Depression is notably associated with higher mortality in this population [31]. Despite increased awareness, however, few structured pathways exist to identify and address these non-physical sequelae. Current pathways involve follow-ups being completed mostly or entirely in person, by the hospital that admitted the patients following their OHCA [12,14]; despite this approach having clear advantages (namely, full access to the clinical history of the patient; patient being already familiar with the hospital/treating team; face-to-face meeting being more accessible to some patients, etc.), it also requires more resources in terms of personnel, training required and clinic space.

The prospective, multicentric REVIVE project aims to investigate the feasibility and acceptability of a centralized, sub-regional system to investigate mood, cognition, fatigue, psychological wellbeing, and overall quality of life at multiple time points up to 12 months post-discharge. It also aims to be the first study to systematically assess psychological distress, cognitive status, and quality of life in a sizable Italian cohort of OHCA survivors.

Study limitations may include attrition (e.g., among patients with cognitive deficits or significant psychological difficulties) and the non-randomized nature of the intervention. Remote/telemedicine follow-up options will aim to reduce dropout; however, they might also constitute a barrier for some patients who feel less comfortable using new technology.

Should the REVIVE study demonstrate the need for a tailored psychological approach and that our approach is feasible and welcomed by the patients, it could serve as a guide to build up similar and permanent programs to help patients thrive and not simply survive after a cardiac arrest.

The results are expected to guide future recommendations on the delivery of follow-up/assessment services and help establish new standards of post-resuscitation care.

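### Retention is counted over all enrolled patients, so a death before month 12 counts against the acceptability of the follow-up service

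*Protocol article*

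**What the plan says.** The design section (2.1) plans to enrol consecutive survivors and "to follow them up for 12 months post-discharge", with the last assessment, T4, at 12 months. Section 2.2 defines retention as "the proportion of enrolled patients who complete scheduled follow-up assessments", taken across the 12 months. Acceptability is then an "overall retention rate of 50% or more of the recruited patients". Both denominators are everyone enrolled, and neither sentence provides for death.

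The same section compares modalities: face-to-face at the main hospital against remote at the others. A "higher attrition rate in the remote modality, as compared to the face-to-face approach, will be interpreted as indicative of reduced feasibility and acceptability"; the sentence is framed in terms of a significant difference. Attrition is not split by cause.

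On missing data, Section 2.4 states: "Missing data will be handled using Multiple Imputation by Chained Equations (MICE), assuming a Missing At Random (MAR) mechanism". It adds: "Participants who completely withdraw from this study will be treated as censored at their last observation without further imputation". Death during follow-up is not mentioned in either section. The Discussion mentions mortality only qualitatively: "Depression is notably associated with higher mortality in this population".

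**The concern.** Acceptability should reflect whether patients who could take part chose to go on. A patient who dies cannot complete T4, whatever he or she thought of the service. Under Section 2.2 that patient counts the same as one who refused. Acceptability is half of the study's first aim, and the 50% threshold is repeated in the abstract, so this is a headline decision rule.

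The modality comparison has the same flaw. Section 2.2 ties modality to hospital: San Matteo is face-to-face and all others are remote. A difference in post-discharge mortality between these hospitals, for instance from case mix, would be read under the stated rule as evidence about remote follow-up.

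**Working it through.** **Inputs from the article.** About 350 eligible survivors over 24 months and 80% consent (Section 3.2): 0.80 × 350 = 280 enrolled, as stated. The threshold is 50% (Section 2.2); no derivation is given for it, so there is none to reproduce.

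**Assumed input.** The article gives no 12-month mortality. I write it as *m* and show 5% to 20%. Retention among survivors is *r*.

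**Step 1: what the rule demands.** Retention as written is r × (1 − m). Setting this to 0.50 gives r = 0.50 / (1 − m).

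| m | Deaths of 280 | Alive | Completers needed as written | Completers needed among survivors | Survivor retention demanded by the written rule |
|---|---|---|---|---|---|
| 5% | 14 | 266 | 140 | 133 | 52.6% |
| 10% | 28 | 252 | 140 | 126 | 55.6% |
| 15% | 42 | 238 | 140 | 119 | 58.8% |
| 20% | 56 | 224 | 140 | 112 | 62.5% |

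At m = 10%, the two definitions disagree if 126 to 139 patients complete. At m = 5%, they disagree for 133 to 139. Outside those counts the verdict is the same.

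**Step 2: chance of passing.** With deaths fixed at 280m and A patients alive, the number of completers X is binomial (A, r). As written, passing needs X ≥ 140. Among survivors, it needs X ≥ A/2.

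| m | True r | Pass, as written | Pass, among survivors |
|---|---|---|---|
| 5% | 52% | 0.443 | 0.763 |
| 5% | 55% | 0.799 | 0.955 |
| 5% | 60% | 0.994 | 1.000 |
| 10% | 52% | 0.143 | 0.758 |
| 10% | 55% | 0.455 | 0.951 |
| 10% | 60% | 0.933 | 0.999 |
| 10% | 65% | 0.999 | 1.000 |
| 15% | 60% | 0.670 | 0.999 |
| 15% | 70% | 1.000 | 1.000 |

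The effect is large just above 50% and disappears as retention rises.

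**Step 3: modality comparison.** Attrition as written is 1 − r(1 − m). If survivors are retained equally in both groups, the difference in attrition is r × (m_remote − m_face-to-face). This is not confined to a band near 50%, and it can go in either direction. Illustration with assumed values r = 70%, mortality 5% face-to-face and 10% remote: attrition is 1 − 0.70 × 0.95 = 33.5% against 1 − 0.70 × 0.90 = 37.0%, a gap of 3.5 points due entirely to deaths. For scale, with an assumed equal split of 140 each, the standard error is √[(0.335 × 0.665 + 0.370 × 0.630) / 140] = 5.7 points. A gap of that size would therefore seldom be significant alone, but it adds to or offsets any real difference.

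**Step 4: late prevalence, if scores after death were imputed.** Prevalence would be (1 − m) × 25% + m × q, where 25% is the planning value in Section 3.2 and q is the prevalence imputed to the dead. With q = 25% there is no shift. With q = 35% the result is 25.5%, 26.0% or 26.5% for m = 5%, 10% or 15%. With q = 50% it is 26.3%, 27.5% or 28.8%. The largest shift, 3.75 points, is below the stated 5-point precision.

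**The case against.** The best defence is that Section 2.2 lists retention under feasibility as well as acceptability. All-cause completion among everyone enrolled is a legitimate and conservative feasibility measure, and a bar as low as 50% leaves room for some deaths. That stands for feasibility. It does not justify using the same figure as the measure of acceptability.

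Second, Section 2.4 plans mixed models for the modality comparison, with covariates such as age, sex and comorbidities and hospital-level random effects. This may absorb part of a case-mix difference. It does not separate death from refusal in the outcome.

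Third, removing deaths needs equal knowledge of deaths. Section 2.1.3 describes survival monitoring through the hospital's electronic system only for San Matteo patients, and the data items named in Section 2.3 do not include vital status after discharge. If deaths were found more completely at San Matteo, removing known deaths would bias the comparison in a new way. This is right, and it shapes the fix.

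A reader might also infer that scores after death will be imputed and that late prevalence is therefore distorted. The text does not establish this:

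- The imputation sentence stands in the paragraph on mixed models. The prevalence paragraph does not mention imputation.
- Withdrawal is not the only special rule for missing data: participants missing both T0 and T1 for an outcome are excluded from its incidence rate.
- Handling of deaths may be set out in a fuller document that is not shown.

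Nor does the Discussion's link between depression and mortality contradict the missing-at-random assumption. Loss that depends on observed depression scores is compatible with it. The sound objection to scores after death is that they do not exist.

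**Conclusion.** The concern holds for the retention definition, which the article fixes. Each death is scored as a failure of acceptability, and the required retention among survivors rises from 50% to 0.50 / (1 − m): 52.6% at an assumed 5% mortality and 55.6% at 10%. The overall verdict can be wrong only when observed survivor retention lies between 50% and that value, and the error is always towards not acceptable. Since the article gives neither mortality nor expected retention, nothing shows that the study will fall in that band, and it would be wrong to say that the verdict is distorted as a matter of fact. The modality comparison is exposed at any retention level, but only if mortality differs between San Matteo and the other hospitals. A distortion of late prevalence is possible but not established; that part is a request for clarification.

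**What to change.** In Section 2.2, for acceptability and for the modality comparison, define retention as completed assessments among enrolled patients alive at the scheduled visit. Report deaths separately by modality. Ascertain vital status at each visit in the same way for all hospitals. Keep completion among all enrolled patients as a secondary, all-cause feasibility figure.

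In Section 2.4, state that death, like complete withdrawal, ends follow-up with no imputation afterwards, and that prevalence at each visit refers to patients alive at that visit.

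The cost is a few sentences and a uniform check of vital status across the hospitals, which is the only real work. No patients are added. The change should be made before retention results are known, because a denominator chosen after seeing a rate close to 50% would not be credible.

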## 3. Expected Results

### 3.1. Investigation of the Feasibility and Acceptability of a Sub-Regional “Hub and Spoke” Model of Post-Discharge Care Delivery

There is growing evidence that management of OHCA in “cardiac arrest centres”, and regionalization of post-cardiac arrest care may be beneficial to improve outcomes ranging from survival to long-term functional abilities (see [30] for a review)—even though there is still no definitive evidence in this area. The feasibility and acceptability of providing post-discharge follow-up care in a centralized manner at a regional/sub-regional level, however, are still unexplored.

Potential benefits of this approach revolve around leveraging the infrastructure, resources, personnel, and experience of a leading high-volume “cardiac arrest centre” to provide high-quality post-OHCA care in line with international guidelines; predictable barriers, however, could be encountered in the acceptability of this service when provided remotely, especially for older people and for those with neurocognitive impairments and/or psychological difficulties. It is expected that REVIVE will help to provide novel evidence in this area to inform the development of new guidelines.

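### Acceptability rests on pooled 12-month retention of 50%, so the rule can be met while most survivors impaired at T0 are lost to follow-up

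*Protocol article*

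**What the plan says.** Section 2.2 defines retention as "the proportion of enrolled patients who complete scheduled follow-up assessments over the 12-month period" and makes acceptability an "overall retention rate of 50% or more of the recruited patients" over 12 months. One breakdown is attached: "this study will look at feasibility and acceptability by follow-up modality". "A significantly lower recruitment rate or higher attrition rate in the remote modality" is to be read as a sign of reduced feasibility and acceptability.

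Section 2.4 follows the same line: "differences in the retention rate between patients seen remotely or face-to-face, will be analyzed using mixed-effects models", "incorporating time and potential covariates (e.g., age, sex, comorbidities" and so on. The covariate list is open, but baseline cognitive or emotional status is not on it.

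Two other places name groups at risk. Section 3.1 says barriers to a remotely provided service could be met, "especially for older people and for those with neurocognitive impairments and/or psychological difficulties". Section 4 says: "Study limitations may include attrition (e.g., among patients with cognitive deficits or significant psychological difficulties".

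The data for a finer split already exist. MoCA, HADS and IES-R are taken at T0 (sections 2.1.3 and 2.3), and section 2.4 fixes cut-offs: MoCA below 26, a HADS subscale above 8, IES-R of 33 or more.

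**The concern.** The purpose of the system is to assess survivors with cognitive and emotional problems and then follow them up to 12 months. The authors name these patients as a group in which acceptability or attrition may be a problem, but the criterion pools everyone recruited. Good retention of unimpaired patients can carry the total past 50% whatever happens to the others.

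At stake is the meaning of the word acceptable. Section 4 says that a feasible approach, welcomed by patients, could guide permanent programmes. A pooled pass would not tell a reader whether the follow-up works for the patients with most need of it.

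**Working it through.** **1. The plan's own figures.** Section 3.2 gives 175 eligible survivors a year: 175 × 2 = 350, and 350 × 0.80 = 280 enrolled. The criterion is therefore met at 280 × 0.50 = 140 patients retained. The article gives no calculation behind the 50%, so there is nothing further to reproduce.

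**2. What the pooled rule allows.** Let *p* be the share impaired at T0, *u* the retention of unimpaired patients and *r* the retention of impaired patients. Overall retention is (1 − *p*)*u* + *p r*. Setting this to 0.50 gives

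*r* = [0.50 − (1 − *p*)*u*] / *p*.

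At exactly 50% overall, *r* is below 50% whenever *u* is above 50%.

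Inputs: *p* = 40–50% is the 6-month rate of cognitive impairment cited in section 1. The article gives no T0 rate, so its use here is an assumption. It gives no retention by impairment status either, so *u* is assumed and shown as a range.

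Impaired retention at which the rule is just met:

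| *p* | *u* = 60% | *u* = 70% | *u* = 75% |
|---|---|---|---|
| 40% | 35.0% | 20.0% | 12.5% |
| 45% | 37.8% | 25.6% | 19.4% |
| 50% | 40.0% | 30.0% | 25.0% |

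For example, with *p* = 40% and *u* = 70%: (0.50 − 0.60 × 0.70) / 0.40 = 0.08 / 0.40 = 20%. In patients, with *p* = 50% and *u* = 70%: 140 × 0.70 = 98 unimpaired patients stay, so 140 − 98 = 42 of 140 impaired patients (30%) are enough.

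Smaller impaired shares give the rule less grip. With *p* = 25% (the 6-month prevalence used for sizing in section 3.2) and *u* = 60%, 210 × 0.60 = 126 unimpaired patients stay, and 14 of 70 impaired patients (20%) suffice. With *p* = 15% (the lower end of the emotional-problem rate in section 1) and *u* = 60%, 0.85 × 0.60 = 51%, so the rule is met with no impaired patient retained.

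**3. Whether the modality comparison would show it.** If impaired patients leave at the same rate under both modalities, and the case mix is similar, attrition does not differ by modality and the comparison shows nothing. Covariates in the section 2.4 model adjust the modality contrast; they do not enter the 50% criterion.

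**4. Whether a split would be informative.** The approximate 95% half-width at 50% retention is 1.96 × √(0.25/*n*): 11.7 points for *n* = 70 (25% of 280) and 8.7 points for *n* = 126 (45% of 280). Exact intervals are slightly wider. Power to compare retention by impairment at two-sided 5%, with overall retention held at 50%:

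- 126 impaired versus 154 unimpaired, 40% versus 58.2%: 86%
- 70 versus 210, 30% versus 56.7%: 98%
- 70 versus 210, 40% versus 53.3%: 49%

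Large gaps would be seen; a modest gap in a small subgroup might not.

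**The case against.** The strongest reply has five parts.

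- **The two warnings are hedged and differ.** Section 3.1 speaks of barriers that could arise with remote delivery and does not mention dropout. Section 4 speaks of attrition that may occur, does not mention older patients, and presents remote options as a means of reducing dropout. A reader might infer that the article predicts the loss of impaired patients. It does not. This stands, and the point needs only that the groups are named.
- **Remote delivery is tested and age is a named covariate.** This is true and partly meets section 3.1. It leaves untouched any loss related to impairment that is common to both modalities.
- **Patients positive at T0 have already been found.** A reader might infer that the system would fail to detect impaired survivors. The documents do not support that: T0 screening identifies them, and section 2.1 provides for in-house support or referral. What is lost is their follow-up. A split by T0 status also does not protect patients whose problems emerge later.
- **The splits are assumed and some are extreme.** Retention of 70% versus 20–30% is an odds ratio of about 5 to 9. That is fair, but 60% versus 35–40% (odds ratio 1.5/0.538 = 2.8 to 1.5/0.667 = 2.25) also just meets the rule while most impaired patients are lost.
- **Comparing completers with dropouts is usual analysis-plan material.** This is true of the model covariates. It is not true of the acceptability criterion, which the article fixes.

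**Conclusion.** The point holds as a limit on what the acceptability criterion can show. The criterion can be met with most patients impaired at T0 lost to follow-up, and neither the modality comparison nor the open covariate list changes the result that it returns. Under an assumed 40–50% impaired at T0 and an assumed 70% retention of unimpaired patients, 20–30% retention of impaired patients is enough.

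This rests on applying a 6-month rate to T0 and on retention values that the article does not give. It describes what the rule permits and is no forecast. An overall retention criterion is not an error or a contradiction in itself.

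A reader might also infer that a second 50% threshold among screen-positive patients is required. It would have no firmer basis than the first, and a subgroup whose true retention was 50% would miss it about half the time. This is a worthwhile, inexpensive improvement to the reporting and to the wording of the conclusion.

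**What to change.** 1. In section 2.2, add that 12-month retention will be reported with exact 95% confidence intervals by baseline status, using the section 2.4 cut-offs (MoCA below 26; HADS subscale above 8; IES-R of 33 or more), and by age group. Use the T1 fallback of section 2.4 where T0 is missing. Show how many patients were classified from T1, since they have by definition completed one follow-up visit, and how many could not be classified.
2. In section 2.4, name baseline status as a predictor in the retention model.
3. State in section 2.2 that overall retention of 50% or more supports acceptability for impaired survivors only to the extent that their own retention estimate and interval support it. Do not add a second pass/fail threshold.

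The cost is wording and a few tables, with no new visit or instrument. Subgroup estimates will be less precise, about 9 to 12 points either side for 70 to 126 patients, and the acceptability conclusion may turn out less favourable.

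### The face-to-face versus remote comparison sets one hospital against all the others, so a significant difference cannot be read as an effect of modality

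*Protocol article*

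**What the plan says.** Section 2.2 (Criteria for Feasibility and Acceptability) sets overall thresholds of 80% recruitment and 50% retention. It then adds an analysis by follow-up modality, "comparing the recruitment and attrition rates between face-to-face assessments at the main hospital and remote assessments at the other hospitals". The decision rule, which takes a deficit as a sign of reduced feasibility and acceptability, follows: "A significantly lower recruitment rate or higher attrition rate in the remote modality, as compared to the face-to-face approach, will be interpreted as indicative".

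Section 2.1.3 (Enrolment and Assessments) ties the baseline mode to the hospital: "either in-person (for patient admitted to Fondazione IRCSS San Matteo hospital, Pavia) or remotely (via telephone call or telemedicine, for all other patients". It also describes different recruitment routes. San Matteo patients are followed in the hospital's own electronic system and approached there. At the ten other main hospitals "the local investigator will approach them for screening and enrollment". For the remainder, "The secondary recruiting centres do not have an allocated local investigator, so they will be contacted as and when required".

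Section 2.1 (Study Design) says that the mode at each time point is chosen "based on patient preference and feasibility".

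Section 2.4 (Statistical Methods) states that "differences in the retention rate between patients seen remotely or face-to-face, will be analyzed using mixed-effects models (linear or logistic"). It adds: "Models will initially include random intercepts and slopes at participant and hospital levels", with a fallback to random intercepts only. It names no model for the recruitment comparison.

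**The concern.** Aim (a) is to learn whether a centralised, largely remote service is feasible and acceptable. Section 2.2 offers a direct test of the remote component, but the two groups are one coordinating centre and everyone else. Anything particular to San Matteo (staff, case mix, case-finding through its own records, contact with the study team) falls on the face-to-face side.

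The reading of a significant deficit is fixed in advance and has no guard against a centre difference. Section 3.1 expects the study to inform guidelines on this model of care, so a difference between hospitals could be reported as evidence against remote delivery.

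**Working it through.** **Plan's own figures.** Section 3.2 gives 175 × 2 = 350 eligible and 350 × 0.80 = 280 enrolled. The precision formula 1.96² × 0.25 × 0.75 / 0.05² gives 288.1, close to 280 (half-width at 280: 5.07 points). This sizing concerns prevalence. No figure is given for the modality contrast.

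**Sections side by side.**

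- If hospital sets the mode (2.1.3 at baseline, 2.2 for the comparison), modality and San Matteo are the same variable. With 11 hospital indicators plus a modality indicator, the design matrix has rank 11 for 12 columns.
- If preference sets the mode (2.1), the hospital split misclassifies mode, and mode is self-selected.
- Neither version supports the rule in 2.2.

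**Recruitment.** Section 2.1.3 places baseline assessment after consent. At the other main hospitals the approach is made by a local investigator, not through the remote assessment. A recruitment gap would therefore mainly measure case-finding and local staffing.

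**Precision for retention under the planned random hospital intercept.** The between-hospital variance is not in the documents. I assume a logit-scale ICC of 0.02 to 0.05 and ten other hospitals (the other main recruiters in 2.1.3).

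- Hospital variance: τ² = ICC/(1 − ICC) × π²/3.
- With unlimited patients, the smallest SE of the log odds ratio for one hospital against k others is τ × √(1 + 1/k).
- ICC 0.02: τ² = 0.0204 × 3.290 = 0.0671, τ = 0.259, SE = 0.259 × √1.1 = 0.272. Limits: exp(±1.96 × 0.272) = 0.59 to 1.70.
- ICC 0.05: τ² = 0.0526 × 3.290 = 0.173, τ = 0.416, SE = 0.436. Limits: exp(±1.96 × 0.436) = 0.43 to 2.35.
- With 21 other hospitals (22 in Section 2.1, less the hub) the multiplier falls only from 1.049 to √(1 + 1/21) = 1.024.

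These are lower bounds on width. For 280 patients, 50% retention (the threshold), an assumed hub share of 20% (56 patients, 22.4 at each of ten others) and τ = 0.25, SE = √[0.0625 + 1/(56 × 0.25) + (0.0625 + 1/(22.4 × 0.25))/10] = 0.398. The interval around no difference is then exp(±1.96 × 0.398) = 0.46 to 2.18.

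**A test that ignores hospital.** This is simulated for recruitment, because no model is named there: 350 eligible, 80% recruitment everywhere, no modality effect, one hospital against ten, hub share 10% to 40% (assumed), 40,000 runs per setting, two-proportion z-test at two-sided 5%.

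| Hospital SD (log-odds, assumed) | Rejects, either direction | Rejects against remote |
|---|---|---|
| 0 | 5% | about 2% |
| 0.25 | 8–16% | 3–8% |
| 0.5 | 19–36% | 9–19% |

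The last column is the relevant one, since the rule in 2.2 acts only on deficits in the remote group. Its nominal level is 2.5%.

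**The case against.** The strongest reply is that this comparison is secondary. Section 2.2 introduces it as an addition, and neither headline threshold nor any prevalence estimate depends on it. Section 2.4 puts hospital effects in the retention model and allows age, sex and comorbidities as covariates. The Discussion lists non-randomisation as a limitation. All of this stands and limits the weight of the point. It does not answer it: covariates do not remove a centre effect, and the limitation does not say that modality coincides with hospital.

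A reader might infer several stronger things that the documents do not support.

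- *That the planned model cannot estimate the contrast.* This is true with fixed hospital effects. A random hospital intercept does return a coefficient, but only by treating San Matteo as exchangeable with the other hospitals.
- *That the planned retention analysis carries the false-positive rates of an unclustered test.* It includes hospital. In a rough linear illustration (150 fits, hospital SD 0.5, 70 hub patients and 21 at each of ten others, some convergence warnings) type I error was about 10%, against 22–40% for the unclustered retention test at that SD.
- *That participant random effects are never identifiable for retention.* If retention is completion at each scheduled visit and visits can be missed intermittently, a participant intercept can be identified. The difficulty arises only with one outcome per patient.
- *That a non-significant result will be read as reassurance.* Section 2.2 interprets only significant deficits.
- *That recruitment has nothing to do with modality.* Some patients may decline because of the follow-up offered. That influence cannot be separated from the site differences.
- *That the mode of contact is not recorded.* The data list in Section 2.3 is not exhaustive, and an article may leave this, like the recruitment model, to the full protocol.

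**Conclusion.** The point holds as a matter of interpretation and internal consistency. The contrast in Section 2.2 is hub against other hospitals and cannot separate modality from centre, recruitment is weak evidence about how assessments are delivered, and Section 2.1 conflicts with Sections 2.1.3 and 2.2 on what determines mode. For retention, even under exchangeability, the odds ratio cannot be pinned down more tightly than about 0.59–1.70 (ICC 0.02) to 0.43–2.35 (ICC 0.05). A recruitment test that ignored hospital would be anti-conservative.

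These sizes rest on the assumed ICC, hospital SD and hub share. The confounding does not. This should be fixed, but it does not threaten the trial's main criteria.

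**What to change.** 1. Reconcile Sections 2.1, 2.1.3 and 2.2 on whether hospital or patient preference determines mode, at baseline and at follow-up.
2. Call the contrast hub versus other hospitals, and delete the rule that a significant difference indicates reduced feasibility or acceptability of the remote modality.
3. Report recruitment and retention differences descriptively, with 95% CIs that allow for between-hospital variation, and state that centre and modality cannot be separated. Do not use recruitment as evidence about assessment modality.
4. Record the mode offered or scheduled at each contact. The mode actually used will not serve, because it is undefined when a contact is missed. Present any within-hub comparison by mode as exploratory and self-selected.
5. If retention is analysed as one outcome per patient, omit participant random effects but keep a hospital term. An ordinary logistic model without hospital would bring back the anti-conservative test.

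The cost is revised wording and, if not already planned, one data field per contact. That field should be settled early, since mode not recorded at the time may not be recoverable. The trial gives up a statement about modality that its design cannot support.
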